### Procedure for unblinding if needed {17b}

Not applicable, since there is no blinding of investigators during the trial and the blinding is intended only for the assessment of primary outcome and data analysis.

## Data collection and management

### Plans for assessment and collection of outcomes {18a}

Most outcomes are collected at baseline, at 13 weeks follow-up, and 1 year after the intervention. Apart from these additional outcomes for physical activity, measurements assessed by accelerometers are collected at baseline, at 6 weeks, at 13 weeks, 6 months after the intervention, and 1 year after the intervention. Data collecting regarding the exercise training sessions are collected at each session and kept in a file where it will be uploaded each week.

All data will be saved in an Easytrial database where data is validated by having 2 individual persons enter data (double entry) and the database will check for inconsistency.

### Plans to promote participant retention and complete follow-up {18b}

Participants are encouraged to continue the exercise training after the intervention. How to implement exercise training as part of their daily life is discussed at all participants’ 13 weeks’ follow-up. Participants are contacted at a 6-month follow-up after the intervention with a visit to receive the accelerometers. Participants are again contacted at 12 months for the last follow-up visit. There is no plan for promoting participant retention.

### Data management {19}

All patient-related information obtained during the trial will be handled by the Danish Data Protection Regulation and the Danish Data Protection Law. The blood samples will be registered from the hospital blood sample portal (Labka), and paraclinical observations will be obtained through EPIC (Epic Systems Corporation). No personal information will be transferred abroad. Collaboration with other Danish Universities will follow the Danish Data Protection Regulation and the Danish Data Protection Law. Personally, identifiable data will be stored in a password-secured web-based clinical trial management system EasyTrial database, which the Danish Data Protection Board has approved under the capital region. Blood samples and MRI scan results will be occurring in the patient files through the EPIC (Epic Systems Corporation).

### Confidentiality {27}

All signed consent forms will be kept in a locked cabinet at the CFAS behind 2 locked doors under the supervision of the primary investigator. Participant data on paper obtained in the trial is kept under the participants’ ID numbers. The de-identified data will be used in the data management and only authorized investigators will be able to access the paper documents. The de-identified data will be kept in a tracked restricted access network drive regulated by the Danish Data Protection Regulation. Publications from this trial will only contain de-identified information about trial participants. Data will not be freely available to other researchers but can be requested in a de-identified dataset to other researchers if found appropriate by the primary investigator.

### Plans for collection, laboratory evaluation, and storage of biological specimens for genetic or molecular analysis in this trial/future use {33}

#### How much and what

Blood will be drawn from the trial participants 5 times. Before the aerobic exercise training intervention, after 13 weeks and at 12 months follow-up, blood drawn before the intervention will be maximum of 300 mL over 2 days. Blood drawn after the intervention will be a maximum of 300 mL over 2 days. At 12 months follow-up, a maximum of 150 mL blood will be drawn. Liver biopsies will be collected before and after the intervention. At each collection, two samples of a maximum of 34.5 mg will be taken. This will include a total of a maximum of 138 mg liver tissue.

#### For what purpose

Some of the blood will be analyzed immediately for general tests like fasting glucose, fasting insulin, lipid status, HbA1c, hemoglobin, leucocytes and differential count, thrombocytes, CRP, ALT, basic phosphatase, LDH, bilirubin, INR, creatinine, carbamide, Na + , K + , creatine kinase, TSH, HBV serology, HBV DNA, HIV, and HCV. Other samples will be saved for analysis after the final participant has finished the trial period. The blood kept for further analysis will be kept in a research biobank at − 80 °C at CFAS. These blood samples will be analyzed for cytokines and hepatokines. Liver biopsies will be used for the histological description of the liver tissue. Any leftover tissue will be kept in a research biobank at the Department of Infectious Diseases, at Copenhagen University Hospital, Hvidovre under regulation by the Danish Data Protection Regulation and the Danish Data Protection Law.

#### Biobank for future research

When all tests are finalized, any excess blood or plasma and liver tissue will be stored in the research biobank at − 80 °C until the trial is finished (October 1st. 2023). After the trial period, the excess samples of blood or plasma, or liver tissue will be moved to a research biobank for future research, where they will be anonymized and stored for a further 10 years after the end of the trial (July 1st, 2033). The biobank for future research will be under the regulation by the Danish Data Protection Regulation and the Danish Data Protection Law. Any future studies that would like to use the biological material will need approval by the Danish Data Protection Regulation and the Danish Data Protection Law.

Trial participants can decline to donate blood for the biobank for future unspecified research without any consequences. Participants can at any time request to have their biological material destroyed. Such a request will lead to immediate destruction.

#### Responsibility and access

Principal investigator will have full access to the material in this period and be responsible for destroying all material after July 1st, 2033. The biological material will not leave Denmark. All regulations by the Danish Data Protection Regulation and the Danish Data Protection Law are kept.

## Statistical methods

### Statistical methods for primary and secondary outcomes {20a}

#### Analysis methods

The primary outcome (fat fraction) will be analyzed using a per protocol analysis according to the predefined compliance criteria. In addition, an intention to treat analysis will be carried out for all participants including those with low compliance. For both analyses, to detect if there is a significant change in liver fat fraction between the intervention and control group, analysis of covariance (ANCOVA) will be used including age, sex, and BMI as covariates. The estimated difference in mean change from baseline to end of the trial between the intervention and control group will be reported together with 95% confidence intervals and *p*-values.

Continuous secondary outcomes will be analyzed using ANCOVA with the same adjustments as for the primary outcome. Estimated differences in mean from baseline to end of the trial between the intervention and control group will be reported together with 95% confidence intervals and *p*-values. Model fit will be evaluated using graphical methods such as residual and QQ plots and, if necessary, outcomes will be log-transformed. For log-transformed outcomes, results will be back-transformed accordingly.

Statistical analyses will be carried out using R (R Core Team, 2021). R: A language and environment for statistical computing. R Foundation for Statistical Computing, Vienna, Austria. URL https://www.R-project.org/.

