### Trial design {8}

This is an investigator-initiated trial that was registered at www.ClinicalTrials.gov before inclusion of the first participant. The trial is designed as a block-randomized, controlled, unblinded, clinical, superiority, exploratory, intervention trial. Thirty persons with CHB and hepatic steatosis are randomized 1:1 to either aerobic exercise training (intervention group, *n* = 15) or no intervention (“do-as-usual” control group, *n* = 15). See Fig. 1 for the study design. The trial will be reported using the CONSORT extension for non-pharmacological treatment interventions [47] and key elements from the REPORT Trial guide [48].

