#### Setting

The exercise training sessions will be carried out at the facilities at CFAS and at the Department of Physical and Occupational Therapy, Copenhagen University Hospital, Hvidovre.

The participants in the control group are instructed to continue their life unchanged and will receive a standard of care in the healthcare system. Standard of care or usual care includes yearly or half-yearly visits to the Department of Infectious Diseases for control of their chronic viral disease with blood tests, fibroscan, and consultation with doctors and nurses. Also, any other treatment participants receive for any other chronic or acute disease at their general practitioner or outpatient clinic. No diet or exercise intervention is offered to the control group.

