### Criteria for discontinuing or modifying allocated interventions {11b}

The participants will be randomly allocated to a group (control /exercise) after the initial baseline test is performed. Sufficient compliance to the exercise intervention is defined by the compliance criteria: Completing ≥ 70% of the 36 exercise training sessions with ≥ 50% of the assigned heart rate max (HR_max_). No participant will be allocated to a different arm after randomization. If a participant is given hepatic steatosis-inducing medicine or diagnosed with HIV/hepatitis C during the trial, they will be taken out of the trial.

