### Methods in analysis to handle protocol non-adherence and any statistical methods to handle missing data {20c}

The primary outcome will be assessed using a per protocol analysis including all participants who complete the compliance criteria defined by as follows: Conducting ≥ 70% of the 36 planned exercise training sessions with ≥ 50% of the assigned heart rate max (HR_max_) assessed by the supervising trainer in the exercise registration. For exercise training sessions where heart rate data is missing (e.g., due to a forgotten watch for supervised exercise training), the exercise training duration will be noted and the participant’s average intensity and time at different intensity zones will be imputed.

Due to the small sample size, missing data will not be imputed.

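### The primary analysis of this superiority trial is per protocol, under a compliance rule that only the exercise arm can fail, so the headline estimate may be biased towards exercise.

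*Protocol article*

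**What the plan says.** The Analysis methods section ({20a}) makes the compliance-restricted set primary: "The primary outcome (fat fraction) will be analyzed using a per protocol analysis according to the predefined compliance criteria". It then adds: "In addition, an intention to treat analysis will be carried out for all participants including those with low compliance". Both analyses use ANCOVA with age, sex and BMI as covariates, and the difference is reported with a 95% confidence interval and p-value. The section on non-adherence and missing data ({20c}) repeats the choice: "The primary outcome will be assessed using a per protocol analysis including all participants who complete the compliance criteria".

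Section {11b} gives the rule: "Sufficient compliance to the exercise intervention is defined by the compliance criteria: Completing ≥ 70% of the 36 exercise training sessions", with at least 50% of the assigned maximum heart rate. Section {20c} adds that this is "assessed by the supervising trainer in the exercise registration", and that intensity is imputed for sessions without heart-rate data. On the comparator, the Setting paragraph says: "No diet or exercise intervention is offered to the control group". Trial design {8} describes the study as a "controlled, unblinded, clinical, superiority, exploratory, intervention trial". No section makes intention to treat primary or says how controls enter the per-protocol set.

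**The concern.** Attendance and training intensity are observed after randomisation. If participants who keep up the programme would have had a more favourable change in liver fat anyway, dropping the others from one arm only puts that difference into the treatment estimate. Adjustment for age, sex and BMI removes only the part of the selection that those covariates explain. In a superiority trial this bias runs towards the hypothesis.

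The setting leaves room for judgement. The trainer who supervises the sessions assesses compliance, and section {17a} accepts that an unblinded primary investigator may assess the outcomes and analyse the data. If the two analyses disagree, the protocol has already named the non-randomised one as primary. The Discussion links a positive result to encouraging or offering exercise in the clinic, and the effect of offering exercise is what intention to treat estimates.

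**Working it through.** **Inputs from the protocol article.** 15 per arm ({8}); SD 2.6 (printed with a minus sign), target difference 2.8 points, 80% power, one-sided 0.05, 14 per group required ({14}); compliance threshold 0.70 × 36 = 25.2, so 26 sessions ({11b}).

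**Assumptions, because the documents give no figure.** k = 2 to 5 of 15 exercisers fail the rule; ρ is the correlation between compliance and a favourable change in liver fat that would have occurred without training.

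**1. The plan's own figure.** n per group = 2(z₁₋α + z₀.₈)²(SD/δ)².
- One-sided: 2 × (1.645 + 0.842)² × (2.6/2.8)² = 10.7, so 11 (12 with the t distribution).
- Two-sided: 2 × (1.960 + 0.842)² × (2.6/2.8)² = 13.5, so 14 (15 with t).

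The stated 14 matches the two-sided formula, although the text says one-sided. That is a separate matter and the present point does not depend on it. Both versions are given below.

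**2. Who can be excluded.** The rule counts training sessions. Exercisers have 36 and controls have none, so applying it can shrink only the exercise arm.

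**3. Bias with no true effect.** If the k least compliant of 15 are dropped, expected bias = ρ × SD × m. Here m is the mean standardised compliance score of those kept, from the expected normal order statistics for n = 15 (lowest five: −1.736, −1.248, −0.948, −0.715, −0.516).
- k = 2: m = (1.736 + 1.248)/13 = 0.230. Bias = 0.3 × 2.6 × 0.230 = 0.18 at ρ = 0.3, and 0.30 at ρ = 0.5.
- k = 5: m = 5.163/10 = 0.516. Bias = 0.40 at ρ = 0.3, and 0.67 at ρ = 0.5.

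A simulation (40,000 null trials per setting, unadjusted t-test) agrees and gives the error rates:

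| ρ | Bias towards exercise, k = 2 to 5 | One-sided 0.05 error | Two-sided 0.05 error |
|---|---|---|---|
| 0 | 0 | 5% | 5% |
| 0.3 | 0.18 to 0.39 points | 7–10% | 5.5–6.6% |
| 0.5 | 0.30 to 0.67 points | 9–16% | 6–10% |

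Intention to treat stays at 5% one-sided throughout.

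**4. Power at the planned effect (noncentral t).** Noncentrality = δ / [SD × √(1/n₁ + 1/n₂)].
- Intention to treat, 15 v 15, full effect 2.8: 89% one-sided, 81% two-sided.
- Per protocol, 11 v 15, effect 2.8: 84% one-sided, 74% two-sided.
- Intention to treat, 15 v 15, with 4 exercisers gaining nothing: difference 2.8 × 11/15 = 2.05; 68% one-sided, 55% two-sided.

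**The case against.** The best defence has three parts. First, the intention-to-treat analysis is already pre-specified with the same model and will be reported, so readers will see the randomised comparison; the fault lies in which analysis is labelled primary. Second, the trial calls itself exploratory, and section {6b} seeks an estimate of the pure effects of exercise, which is an explanatory question. Third, sessions are supervised and adherence is actively supported, so few exercisers may fail the rule. All three soften the consequence. None makes a comparison of selected exercisers with all controls a randomised one, or isolates the pure effect from selection.

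A reader might infer more than the documents support:
- **That the type I error is necessarily inflated.** It is not if compliance is unrelated to outcome, and the simulation does not include the planned covariate adjustment.
- **That compliers are a fitter group.** No section says so.
- **That no control could enter the per-protocol set.** Read literally, {20c} suggests this, but {11b} defines compliance with the exercise intervention, so the sensible reading keeps every control. The text should still say so.
- **That controls who take up exercise add to the bias towards exercise.** They would narrow the contrast and work against the intervention.
- **That per protocol leaves the trial underpowered.** On the one-sided test in {14}, 11 v 15 still has 84%.

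**Conclusion.** The point holds. Two sections make per protocol primary, the rule can remove participants from one arm only, and no other text corrects this. The headline estimate may therefore favour exercise. Under the assumptions above the bias ranges from nothing to about 0.7 points, at most about a quarter of the 2.8-point target (0.67/2.8 = 24%), with one-sided error between 5% and 16%. Neither the exclusion rate nor the correlation can be taken from the documents, so these figures illustrate a range and do not predict what will happen. The change is still needed, because the label decides which result is the trial's answer and the randomised alternative is already planned.

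**What to change.** In sections {20a} and {20c}:
- Make intention to treat the primary analysis: all randomised participants with outcome data, as allocated, whatever their attendance. The reference to outcome data is needed because the plan does not impute missing values.
- Make per protocol supplementary, label it a non-randomised comparison, and state that all controls are kept in it.

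**Cost.** No new data are needed. The wording changes in the protocol, any analysis plan and the registry entry. The change is credible only if made before results are seen; the Trial status section reports 13 recruited by January 2023, with recruitment planned to end in June 2023. The real price is dilution. The protocol should state that non-compliance lowers the expected intention-to-treat difference and its power (step 4 of the check). With 15 randomised per arm against 14 required and no stated allowance for non-compliance, the sample size section should be reviewed in that light.

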### Sample size {14}

The sample size for the primary outcome was calculated in relation to the fat fraction of the liver. To our knowledge, no-exercise intervention studies have been performed in patients with CHB. We used exercise training intervention studies in non-alcoholic-fatty liver disease (NAFLD) or sedentary, dysglycemic patients with measurements of MRI measurements of intrahepatic lipid content as the fat fraction to calculate the sample size. The one-sided test is chosen due to the current literature, which states that exercise training intervention generally reduces the fat fraction of the liver and does not increase the fat fraction of the liver [36, 61–63]. Assuming a SD of − 2,6 [36] and no change in the control group. An 80% chance of detecting a − 2.8% between-group change in liver fat fraction with a one-sided 0.05 significance requires *n* = 14 in each group.

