## Assignment of interventions: allocation

### Sequence generation {16a}

Randomization 1:1 is done using https://www.sealedenvelope.com/simple-randomiser/v1/lists with varying block randomization. No stratification is used.

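### The ANCOVA lists age, sex and BMI but not the outcome's own baseline value, and does not name the response; adding baseline is a cheap gain in precision

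*Protocol article*

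**What the plan says.** The Analysis methods section gives one model for both the per-protocol and the intention-to-treat analysis of liver fat fraction: "analysis of covariance (ANCOVA) will be used including age, sex, and BMI as covariates". The contrast is a change: "The estimated difference in mean change from baseline to end of the trial between the intervention and control group will be reported". For the rest, "Continuous secondary outcomes will be analyzed using ANCOVA with the same adjustments as for the primary outcome". Model fit is to be checked graphically and, "if necessary, outcomes will be log-transformed", with results transformed back.

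No sentence says whether the dependent variable is the week-13 value or the change. No section of the article adds the baseline value of the outcome as a covariate. That value will be known before allocation: the Abstract places an MRI scan before the intervention, and Implementation {16c} has the envelope opened at the end of the baseline examinations.

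On design, Trial design {8} states "Thirty persons with CHB and hepatic steatosis are randomized 1:1", that is, 15 per arm, and calls the trial exploratory. Sequence generation {16a} adds "No stratification is used".

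**The concern.** Read literally, the text leads an analyst to fit change on group, age, sex and BMI. Subtracting the baseline removes it fully only if a one-point higher baseline predicts a one-point higher follow-up value. With an imperfect correlation, participants who start high tend to fall further, so an arm that starts higher by chance appears to improve more. With 15 per arm and no stratification, such imbalance is not rare. Variation explained by baseline also stays in the residual and widens the confidence interval.

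Two features of this trial sharpen the point. First, the lead analysis is per protocol, and its compliance rule concerns attendance and heart rate at training sessions. It can therefore remove participants from the exercise arm only, and randomisation does not protect baseline balance in what remains. Second, the response is not named. If the analyst takes the week-13 value and adjusts only for the three listed covariates, baseline is neither subtracted nor modelled, and the loss is greater.

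**Working it through.** **Inputs from the protocol.** 30 participants, 1:1; target "2.8% between-group change in liver fat fraction with a one-sided 0.05 significance"; 80% power; SD 2.6; no change in controls (Sample size {14}).

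**Assumptions.** 2.6 is the SD of change (the section does not say so). Baseline and week-13 variances are equal. The baseline to week-13 correlation rho is not given, so 0.5 / 0.7 / 0.9 are shown. Age, sex and BMI are treated as uninformative. All 30 are analysed.

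**The plan's own figure.** n per arm = 2 × (z_alpha + z_beta)² × SD² / d², with 2 × 2.6² / 2.8² = 1.7245.
- One-sided 0.05: 1.7245 × (1.645 + 0.842)² = 10.7, so 11 per arm (12 with the t distribution).
- Two-sided 0.05: 1.7245 × (1.960 + 0.842)² = 13.5, so 14 per arm (15 with t).

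The stated 14 per group equals the two-sided normal result; the stated one-sided inputs give 11 to 12. The present point does not depend on this, and both kinds of test are shown below.

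**Chance imbalance.** The standard error of a baseline difference is s × √(2/15) = 0.365 s, where s is the SD of a single measurement. The chance of a difference above 0.5 s in either direction is 2 × [1 − Φ(0.5 / 0.365)], about 17%.

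**What remains in a change score.** s = 2.6 / √(2(1−rho)). A one-SE imbalance shifts the change-score estimate by (1−rho) × SE, in favour of the arm that starts higher. For an unadjusted week-13 value the shift is rho × SE.

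| rho | s | SE of imbalance | shift, change score | as % of 2.8 | shift, week-13 value |
|---|---|---|---|---|---|
| 0.5 | 2.60 | 0.95 | 0.47 | 17% | 0.47 |
| 0.7 | 3.36 | 1.23 | 0.37 | 13% | 0.86 |
| 0.9 | 5.81 | 2.12 | 0.21 | 8% | 1.91 |

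**Precision.** Adding baseline to a change-score model multiplies the residual variance by (1+rho)/2 = 0.75 / 0.85 / 0.95. The extra covariate has a price: chance correlation between covariates and group inflates the variance of the treatment estimate by about (N−3)/(N−k−3) for k covariates. Going from k = 3 to k = 4 with N = 30 costs a factor 24/23 = 1.043. The net variance ratio is 0.75 × 1.043 = 0.78, 0.85 × 1.043 = 0.89 and 0.95 × 1.043 = 0.99. Simulation agrees to within about 0.01.

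**Power by simulation** (15 per arm, difference 2.8, SD of change 2.6, three uninformative covariates):

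| rho | two-sided, without → with baseline | one-sided, without → with baseline |
|---|---|---|
| 0.5 | about 76% → 86% | about 86% → 92% |
| 0.7 | about 76% → 81% | about 86% → 89% |
| 0.9 | about 76% → 77% | about 86% → 86% |

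Charging each covariate only its degree of freedom (25 without baseline, 24 with it) gives higher two-sided figures, 80.9% rising to 90.4% / 86.6% / 82.7%. These are too optimistic because they leave out the variance inflation.

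**If the response is the week-13 value.** Adding baseline multiplies the residual variance by 1 − rho² = 0.75 / 0.51 / 0.19, or about 0.78 / 0.53 / 0.20 after the factor 1.043.

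**The case against.** The strongest defence is that ANCOVA of a before-and-after outcome is commonly understood to include the baseline value. The sentence says which covariates are included, not that there are no others, and a fuller analysis plan may settle it. That stands as far as it goes: a reader might infer that baseline has been deliberately excluded, and the text does not show that. But three covariates are named, the same set is carried to the secondary outcomes, and the obvious one is absent. An analyst working from this text alone would leave it out.

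Other strong readings do not survive:
- **Chance imbalance is left wholly uncorrected.** Not if change is the response. Subtraction removes most of it when rho is high, leaving (1−rho) times the imbalance, in either direction.
- **The analysis is invalid or the trial underpowered.** The intention-to-treat change-score estimate is unbiased over randomisations. At the one-sided level of the sample-size section, power without baseline is about 86% under the assumptions above, already beyond the planned 80%.
- **Baseline is the strongest predictor of change.** The document gives no figure for this. Under the model above, baseline explains (1−rho)/2 of the variance of change: 25% / 15% / 5%.
- **The log fallback fails because a fall in fat is negative.** This assumes that the difference itself is logged. The text speaks of logging outcomes, and the listed outcomes are measured values; the difference of two logs is well defined and transforms back to a ratio.

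**Conclusion.** The point holds as a worthwhile, inexpensive improvement, not as a flaw that invalidates the analysis. The article fixes a covariate list without the outcome's own baseline and does not name the response.

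If change is the response, the cost in the intention-to-treat analysis is modest precision and a conditional bias of about 0.2 to 0.5 points for a one-SE imbalance. The benefit of adjustment runs from useful at rho 0.5 (about 10 percentage points of two-sided power) to essentially nil at rho 0.9. It also depends on reading 2.6 as the SD of change, on equal variances, and on age, sex and BMI carrying little information; if they correlate with liver fat, they would absorb part of the imbalance.

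The case is stronger in two settings: the lead per-protocol set, where imbalance need not be due to chance alone, and an analysis of the unadjusted week-13 value.

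**What to change.** Before analysis, state the response and add each outcome's own baseline value as a covariate, in the primary model (both analysis sets) and in every continuous secondary model. For example: week-13 value on group, baseline value, age, sex and baseline BMI. With baseline in the model, the treatment estimate is the same whether the response is the week-13 value or the change, so the planned contrast can still be reported.

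Where a log scale is needed, model log(week-13) with log(baseline) as covariate and report a ratio of geometric means.

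The cost is one degree of freedom and about 4% variance inflation, which roughly cancels the gain if rho is near 0.9. No new data are needed. Adjustment will not remove every selection effect in the per-protocol set, only the part carried by baseline. Because the article allows that outcome assessment and analysis may be unblinded, the model should be fixed in writing before outcome data are examined.
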